### Interim analyses {21b}

Not applicable.

### Methods for additional analyses (e.g., subgroup analyses) {20b}

Not applicable.

### Methods in analysis to handle protocol non-adherence and any statistical methods to handle missing data {20c}

This multicenter, randomized, controlled superiority trial will compare DT versus ST GR for all allocated patients with available data, on an intention-to-treat basis. A generalized linear mixed model could be used to compare the two groups with regard to the 10MWT speed or secondary outcomes.

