#### Secondary outcome measures

The secondary outcomes measures will be (i) motor performance (lower limb motricity, gait, and balance), (ii) cognitive performance, (iii) autonomy, (iv) disability, and (v) QoL in the short, medium, and long term after stroke, as a function of gait characteristics and post-stroke plasticity. In order to evaluate short-, medium- and long-term effects, these outcomes will be assessed at M1, M2, and M6, respectively. The classification of the various gait characteristics at baseline will describe the epidemiology of gait disorder phenotypes at the sub-acute stroke stage.

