#### Secondary outcome measures

The secondary outcomes measures will be (i) motor performance (lower limb motricity, gait, and balance), (ii) cognitive performance, (iii) autonomy, (iv) disability, and (v) QoL in the short, medium, and long terms after stroke, as a function of gait characteristics. In order to evaluate short-, medium- and long-term effects, these outcomes will be assessed at M1, M2, and M6, respectively.

Pre-study training visits will ensure that each center's personnel are trained in the study requirements, standardized measurement, counseling for adherence, and the collection of information from the study participants in a uniform, reproducible manner. The data will be collected in an electronic case report form (e-CRF), and the procedures to be implemented at each visit will be reviewed in detail in the SYNCOMOT manual. Each of the data collection forms and the nature of the required information will be discussed in detail on an item-by-item basis. Entering data forms, responding to data discrepancy queries, and obtaining research-quality data will also be covered during the training session.

The study manual will include details of SYNCOMOT's procedures and the equipment used, in order to standardize clinical practice during the assessments at M0, M1, M2, and M6. Manuals and monitoring visits will increase the data quality and ensure that the centers will not deviate from the protocol.

Data from the e-CRF will be securely transmitted and quality controlled in the same manner as the core data from the coordinating center. Ennov Clinical® data entry software will instantly identify any missing or aberrant data, so that the latter can be completed or corrected as soon as possible.

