### Plans to promote participant retention and complete follow-up {18b}

SYNCOMOT is an in-patient protocol; retention is therefore expected to be high because (i) the included patients will be hospitalized in a stroke rehabilitation unit during their GR, and (ii) follow-up at M6 is a routine clinical procedure after stroke. Any deviation from the study protocols will be reported in the e-CRF by training therapists. The Ennov Clinical® data entry software will instantly identify any missing or aberrant data, so that the latter can be completed or corrected as soon as possible. This multicenter, randomized, controlled superiority trial will compare DT versus ST GR programs for all allocated patients with available data, on an intention-to-treat basis.

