## Statistical methods

### Statistical methods for primary and secondary outcomes {20a}

#### Primary outcome measure

The primary outcome measure will be the ST 10MWT result 5 months after the end of the GR protocol. Depending on the type of data and after adjustment for the patient’s age, center and the NIHSS score in an analysis of covariance (ANCOVA), an independent *t*-test, a Mann-Whitney test, or a generalized linear mixed model will be used to compare the two groups with regard to the 10MWT speed.

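### An available-data comparison is labelled intention-to-treat, and the mixed model that could use the M1 and M2 speeds of patients without an M6 speed is left optional

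*Protocol article*

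**What the plan says.** The section on non-adherence and missing data {20c} says that the trial "will compare DT versus ST GR for all allocated patients with available data, on an intention-to-treat basis". The retention section {18b} repeats the rule: the trial "will compare DT versus ST GR programs for all allocated patients with available data, on an intention-to-treat basis".

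The next sentence of {20c} adds: "A generalized linear mixed model could be used to compare the two groups with regard to the 10MWT speed or secondary outcomes".

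Under Statistical methods {20a}, the primary endpoint is a single late value: "The primary outcome measure will be the ST 10MWT result 5 months after the end of the GR protocol". For the comparison, after ANCOVA adjustment for age, center and NIHSS and depending on the type of data, "an independent *t*-test, a Mann-Whitney test, or a generalized linear mixed model will be used to compare the two groups". Neither section says which visits the mixed model would include.

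Table 3 schedules the single-task 10-m walk test at M0, M1, M2 and M6. The Outcomes section {12} says of the secondary outcomes, gait among them, that "these outcomes will be assessed at M1, M2, and M6, respectively".

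The article plans for a 10% loss to follow-up with 300 patients included (Recruitment {15}).

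**The concern.** Analysing patients as allocated, but only where data exist, meets one half of intention-to-treat. The other half, that every randomized patient counts toward the result, is not met. A reader of the eventual report would take the label to promise more protection against selective loss than the rule gives.

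The menu of methods makes this matter. A t-test, a Mann-Whitney test or an ANCOVA on M6 alone uses only patients with an M6 speed. A mixed model fitted to all post-baseline visits also uses patients seen at M1 or M2 but not at M6. So the later choice of test decides who is analysed, and that choice is tied only to the type of data. Naming a mixed model does not settle it either, because such a model can be fitted to M6 alone, for example with center as a random effect.

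At stake is the M6 difference in speed. If slower walkers are more often missing, and more so in one arm, an available-data comparison shifts that difference. The trial is open and its assessors are not blinded ({17a}), so loss that differs by arm cannot be ruled out.

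**Working it through.** **Inputs from the article.** Target difference 0.1 m/s, SD 0.3 m/s, two-sided alpha 0.05, power 80%, 280 evaluable (140 per arm) (Sample size {14}); 10% loss, 300 included (150 per arm) (Recruitment {15}).

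**Inputs that are assumptions.** Missing shares by arm, the speed gap between observed and missing patients, and the correlation between M2 and M6 speed. The article gives none of these, so ranges are used.

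**1. The plan's own figure.** n per arm = 2 × (1.960 + 0.842)² × 0.3² / 0.1² = 141.3, rounded up to 142, or 284 in total. The stated 280 is within 2% of this; power at 140 per arm is 79.6%. The figure reproduces.

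**2. What an M6-only comparison leaves.** 150 × 0.90 = 135 per arm. Power = Φ(0.1 / (0.3 × √(2/135)) − 1.960) = Φ(2.739 − 1.960) = Φ(0.779) = 78.2%. Like the article's calculation, this ignores any gain from covariate adjustment.

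**3. Bias of the available-data difference.** Within an arm, the observed mean equals the full mean plus p × g, where p is the missing share and g is the mean M6 speed of observed patients minus that of missing patients. With the same g in both arms, the bias of DT minus ST is (p_DT − p_ST) × g.

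- 10% and 10%, any common g: 0.
- 8% DT and 12% ST, g = 0.2: −0.04 × 0.2 = −0.008 m/s.
- 8% and 12%, g = 0.6: −0.04 × 0.6 = −0.024 m/s.
- 5% and 15%, g = 0.2: −0.10 × 0.2 = −0.020 m/s.
- 5% and 15%, g = 0.6: −0.10 × 0.6 = −0.060 m/s.

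The size runs from 8% to 60% of the 0.1 m/s target. The sign reverses if the DT arm has the greater loss. All these scenarios average 10% missing, as planned.

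**4. What the earlier visits recover in precision.** If values are missing completely at random and M2 speed has correlation r with M6 speed, the variance of an arm mean that uses M2 is about (SD²/135) × (1 − 0.10 r²). The effective n per arm is then 135 / (1 − 0.10 r²).

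- r = 0.7: 135 / 0.951 = 142.0, power 80.2%.
- r = 0.9: 135 / 0.919 = 146.9, power 81.5%.

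The gain over 78.2% is small. The case for the longitudinal model is mainly about bias.

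**5. Illustration by simulation.** Assumed: true difference 0.10 m/s, M2–M6 correlation 0.85, 150 per arm, 5% missing in DT and 15% in ST, with 90% of the missing expected among the slowest 30% at M2. Over 2,000 replicates the available-data difference averaged 0.070 m/s, and an estimate using the M2 speeds averaged 0.101 m/s. Missingness here depends on M2 speed alone, so the recovery is the best case for using that visit.

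**The case against.** **The mixed model is already in the plan.** It is among the methods in {20a} that are to be used, and it reappears straight after the available-data sentence in {20c}. A patient with M1 and M2 speeds does have available data under a longitudinal model. This stands: the plan does not fix a complete-case analysis. But it does not rule one out, and nothing says that M1 and M2 would enter the model.

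**This is a journal article, and an analysis plan may exist.** Imputation details and sensitivity analyses can properly sit there, and none is asked for here. The label and the open choice of test, however, are statements that the article makes, not details that it leaves out.

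**Retention is expected to be high.** {18b} argues from inpatient treatment and routine M6 follow-up. The first argument covers the four-week program rather than the months after it. The second helps, yet {15} still plans for 10% loss.

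**The bias is not demonstrated.** It rests on assumed arm differences and speed gaps and is zero when both arms lose equally with the same gap. This stands.

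**The M1 and M2 speeds are not discarded.** They are analysed as short- and medium-term outcomes. What is lost under the simpler options is their use for the M6 comparison.

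**A stronger reading is tempting:** that patients who can no longer walk at M6 are excluded. The article does not say so. It is silent on whether they are omitted, scored or modelled, and exclusion is only an inference from the reference to available data. Nor does the point require scoring them 0 m/s. That would change the quantity being estimated, and it is costly: with 2% non-walkers in each arm (assumed) around a mean of 0.84 m/s, the SD rises from 0.30 to 0.32 and power at 150 per arm falls to about 76%.

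**Conclusion.** The point holds in a limited form. The intention-to-treat label overstates an available-data set. The primary analysis may also turn out to be an M6-only test that omits every randomized patient without an M6 speed, although earlier speeds are scheduled for the same patients. A reader might infer that a complete-case analysis is prescribed, but the text only leaves one open.

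The possible bias is about 0.008 to 0.06 m/s against the 0.1 m/s target. It arises only if missingness is related to walking speed and differs between arms as assumed. The precision at issue is modest: about 78% power against 80% to 82%, under the assumed correlations. This should be changed because a better method is available at little cost, not because the result is shown to be wrong.

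**What to change.** In {20a} and {20c}, replace the choice among tests with one primary analysis: a longitudinal mixed model of single-task 10-m walk speed at M1, M2 and M6 for all randomized patients, as allocated. Include baseline (M0) speed, age, NIHSS, center, and arm by visit, and make the M6 contrast the primary comparison.

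In {18b} and {20c}, describe the analysis set as it is instead of calling the available-data set intention-to-treat. With M0 speed as a covariate, a patient with no post-baseline speed adds nothing to the estimate, and the description should say so.

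The cost is a change of wording and modest extra programming, with no new data. The model relies on speeds being missing at random given the earlier speeds and covariates. This is weaker than what an M6-only comparison needs, but it cannot be verified from the data.

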### Plans to give access to the full protocol, participant level-data and statistical code {31c}

SYNCOMOT’s full protocol (Tables 1, 2, and 3) and datasets during and/or analyzed during the current study are available from the corresponding author on reasonable request. The participant-level dataset will be accessible only to the coordinating investigator, the relevant health authorities (for official inspections), or representatives duly appointed by the sponsor (for quality audits) via an individual, secure online connection (personal login and password) via Ennov Clinical® software. The datasets analyzed during the present study will be available from the corresponding author on reasonable request.

## Oversight and monitoring

### Composition of the coordinating center and trial steering committee {5d}

The study is sponsored by Amiens Picardie University Medical Center. The coordinating investigator is the head of the medical center’s neurological rehabilitation department and will train the investigators at the other investigating centers. The DRCI will host the study’s steering committee (comprising a clinical research associate, a methodologist, a data manager, a biostatistician, a physical medicine and rehabilitation physician, and a project manager). The coordinating investigator (a physical medicine and rehabilitation physician) and the DRCI will provide day-to-day organizational support and study monitoring. The steering committee represented by clinical research associate and coordinating investigator will meet at the beginning and the end of the trial at each center and on request as needed. Implementation and monitoring visits at all investigating centers will be performed as required, and inclusion curves will be circulated as needed.

### Composition of the data monitoring committee, its role and reporting structure {21a}

The study data monitoring committee will comprise a clinical project manager, a data manager, and a clinical research associate from the DRCI, none of whom have conflicts of interest. The funding body has no role in the study design or the collection, analysis, interpretation, and presentation of the study data.

### Adverse event reporting and harms {22}

Adverse events might include falls, fatigue, headache, or other medical events after inclusion. All adverse events (even those not necessarily associated with the intervention) will be recorded on the participant's individual electronic case report form at each study visit. A safety report will be sent to the pharmacovigilance unit and the study sponsor once a year. Serious adverse events will be reported to the study sponsor within 48 h; the latter will then inform all the investigating centers.

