### Intervention description {11a}

GR program is based on a personalized, progressive DT approach; with repetitive, goal-oriented tasks. At each site, at least two trained physiotherapists will deliver the intervention in the two parallel groups. The GR sessions will include 30 min of physical therapy on 3 days a week for 4 weeks after inclusion (i.e., 12 sessions in total), instead of the patient’s standard rehabilitation sessions on those days. Each 30-min session will consist of five different 5-min exercises, with 1 min of rest between each exercise. The GR protocols will focus on ST gait or on cognitive-motor DT gait. The patient’s progression through the protocol will be standardized according to the self-assessed cognitive and motor burdens (rated on visual analog scales (VASs)) at the end of each session. If the cognitive or motor burden of the last session is below 7 on the VAS, the intensity in the next session will be incremented by one level. Ideally, the intensity of the patient’s GR will increase week after week. If the patient fails an exercise or session, it will be replaced by the last exercise or session in which the patient was successful. The sessions’ functional task training will combine intensity with functional relevance [16]. The care providers’ adherence to the rehabilitation protocol will be evaluated during study monitoring visits.

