### Strategies to improve adherence to interventions {11c}

Included patients will join the SYNCOMOT in-patient rehabilitation program in each participating center. The GR rehabilitation protocols will be gradual and personalized, in order to motivate the participants. Trained therapists will ensure that the patients comply with the GR protocol in each session. The level(s) of difficulty (the motor burden and/or the cognitive burden) during the two GR programs will be self-assessed by the patient on VASs at the end of each session and recorded by the therapist. Depending on the patient's progression through the GR protocol, up to 12 intensity levels can be performed. If a patient fails an exercise or session, she/he will repeat the last successfully completed exercise or session. If an exercise is not possible, an alternative exercise will be provided in the protocol and thus will ensure that the patient performs 30 min of GR. If the GR protocol is suspended because of an acute health problem, the 30-min sessions will be rescheduled so that all twelve 30-min training sessions are completed within 31 days.

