The study's future results might open up perspectives in the field of rehabilitation. The cognitive effects of DT rehabilitation might be of value for patients because cognitive impairment is one of the main determinants of post stroke disability [7, 87]. It has been estimated that respectively two thirds and one third of patients have subjective memory complaints and objective memory impairments 21 months post-stroke [48, 88]. These cognitive impairments have a negative effect on the patient’s functional independence [49]. The long-term efficacy of cognitive rehabilitation protocols is subject to debate, even though this question has been extensively studied [24, 57, 58]. Assessment of the relationship between the patients’ gait classification and post-stroke impairments might open up other perspectives. This classification identifies quantitative and qualitative differences according to the phenotype of gait and might help to target the GR program on specific disorders. We hope that a structural and functional neuro-imaging analysis of post-stroke plasticity will help us to better understand the neuronal networks involved in motor and cognitive recovery. Although researchers have applied the capacity-sharing, bottleneck, and cross-talk theories to CMI and its neural correlates in humans, further studies are needed [33]. Our findings are likely to be transferable to the clinic because a DT GR program could be adapted for easy, routine use with inpatients and outpatients after stroke or with other neurologic diseases.

This novel study of the sub-acute post-stroke period onwards is intended to help patients recover ecological gait skills; independent walking is essential for activities of daily living and for social inclusion. The ability to engage in a concurrent cognitive task while walking is impaired after stroke and needs specific rehabilitation. A DT GR program might increase the interaction between cognitive and motor functions and thus improve personal autonomy, social participation, and QoL. The interaction between cognitive function and gait is a fascinating area of research with practical clinical implications in neurological diseases and aging. Independent living in the community is important for decreasing the stroke burden for patients and for society.

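### Non-serious adverse events, falls included, are scheduled for recording only at M1, M2 and M6, although therapists already complete a record at every training session

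*Protocol article*

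**What the plan says.** Section {22} of the protocol article, on harms, states what is expected: "Adverse events might include falls, fatigue, headache, or other medical events after inclusion". It then fixes when events are entered: they go on the participant's "individual electronic case report form at each study visit", whether or not they are linked to the intervention. Serious events have a separate sentence: "Serious adverse events will be reported to the study sponsor within 48 h".

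Table 3 gives the schedule. The row for adverse and serious adverse events is ticked at M1, M2 and M6 and sits in the investigator's block. The therapists' block lists only the walking and timed up-and-go tests.

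Therapists do keep other records as training proceeds. Under section {11c} the difficulty of the programme is "self-assessed by the patient on VASs at the end of each session and recorded by the therapist". Under section {18b}, "Any deviation from the study protocols will be reported in the e-CRF by training therapists". Section {19} has therapists collect data on paper forms and enter them in the e-CRF. None of these sections mentions adverse events. Section {11a} sets the training dose at "30 min of physical therapy on 3 days a week for 4 weeks after inclusion (i.e., 12 sessions in total".

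**The concern.** Falls are the harm one would most want to compare between these arms. Both programmes use obstacles, foam surfaces and fast walking in people selected for slow gait after stroke. The dual-task arm adds a concurrent cognitive or manual task. Whether that costs extra falls is the obvious safety question, and the Introduction itself treats falls as a major problem after stroke.

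The stated schedule gives that question three recording points, the last of them 4 months after the one before. Someone on the study team fills in a form at every session, but that form is not stated to carry a fall entry. A departure from protocol in a session thus has a stated therapist route into the e-CRF, while a non-serious fall in the same session does not.

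What is at stake is the completeness of the safety comparison. If minor falls are missed, the trial could report similar fall counts in the two arms with less information behind that statement than it could easily have had. The trial is open and section {17a} says the outcome assessors are not blinded, which is a further reason to prefer prompt, structured capture to later entry.

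**Working it through.** The plan gives no figure to reproduce here, so the check sets the recording schedule against the session schedule.

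**Inputs**
- Visits: M0 at inclusion, M1 at the end of training, M2 one month later, M6 five months after the end of training (Abstract, Table 3).
- Adverse-event entries: M1, M2 and M6 (Table 3).
- Training: 12 sessions over 4 weeks (section {11a}), or within 31 days if suspended for an acute health problem (section {11b}).
- Planned enrolment: 300 patients (section {15}).

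**Gaps between scheduled adverse-event records** (later visit minus earlier visit, at 30.44 days per month)

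| Interval | Months | Approximate length | Scheduled contact inside the interval |
|---|---|---|---|
| M0 to M1 | 1 − 0 = 1 | 4 weeks of training, up to 31 days | 12 therapist sessions |
| M1 to M2 | 2 − 1 = 1 | 30 days | none stated |
| M2 to M6 | 6 − 2 = 4 | 4 × 30.44 ≈ 122 days (17.4 weeks) | none stated |

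The last interval is 4/6, or two thirds, of the 6 months of follow-up.

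**Sessions concerned.** 300 patients × 12 sessions = 3,600 planned sessions. Each has a therapist record, and none of those records is stated to include adverse events.

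**Effect of using the session record.** Average interval between records during training: 28/12 ≈ 2.3 days, or 31/12 ≈ 2.6 days if training stretches to 31 days. At present there is one record after about 4 weeks. The M2 to M6 gap stays at about 122 days, because no sessions take place after M1. That interval needs its own remedy.

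**What cannot be computed.** The document gives no expected fall rate and no proportion of falls likely to be missed, so no size or direction of under-count follows from it.

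**The case against.** The strongest reply is that the text fixes when the e-CRF is completed and not where the information comes from. Patients are in hospital during training (section {18b}) and a therapist delivers each session, so a fall in a session happens in front of staff, and the M1 entry can draw on them or on the chart. A reader might infer that training falls depend on patients' memory. The document does not say so, and for the training period the inference is weak. What stands is that entry is retrospective by about a month and its source is not stated.

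A reader might also infer that the 48-hour report of serious events cannot work if events surface only at visits. That is not supported. The 48-hour duty stands alone and is not tied to a visit, so an injurious fall that qualifies as serious has its own route. When the 48 hours start is a detail that a condensed article may leave to the full protocol.

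The Discussion says "two thirds and one third of patients have subjective memory complaints and objective memory impairments 21 months post-stroke", and it is tempting to apply this to the trial's patients. It is cited background at 21 months. Participants here are enrolled within 6 months of stroke, must be able to consent, and are excluded for severe aphasia. The figure says nothing about their ability to report falls.

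Unequal under-counting by arm is possible in an open trial, but no direction can be derived, and the Discussion says the same care providers treat both groups.

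Finally, the article condenses a fuller protocol, and section {18a} refers to a study manual that may describe the forms. That is a fair limit on any claim about what the session form contains. It does not remove the schedule, which the article states outright in section {22} and Table 3.

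**Conclusion.** The point holds for non-serious adverse events. Their recording is scheduled only at M1, M2 and M6, with gaps of about 1, 1 and 4 months. The record kept at each of the 12 sessions is not stated to include them. The weakest stretch is M2 to M6, where no contact is scheduled for about 122 days and under-capture of non-serious falls is most plausible. During training the issue is milder: events are likely to be observed, but there is no stated prompt entry for them.

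This is a design choice that can be improved cheaply. It is neither an error of calculation nor a contradiction. It leaves the primary comparison of gait speed untouched and limits only the between-arm comparison of harms. The conclusion assumes that the session record and the visit schedule are as the article describes them. If the full protocol or manual already has therapists log adverse events per session, only the M2 to M6 part remains.

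**What to change.** 1. Add one line to the existing session record in both arms: adverse event or fall, yes or no, during the session or since the last one, with or without injury. Enter it in the e-CRF by the same therapist route as other session data.
2. Give each patient a dated fall calendar at M2, to be returned at M6. The session line does nothing for this interval.
3. Report falls by arm, separately for the training period and for follow-up.
4. Introduce the change in both arms on the same date, and state in the report which patients have visit-only data.

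**Cost.** A few seconds per session, one e-CRF field, a printed calendar and more minor events to enter. No extra visits or staff are needed. The main drawback is mixed capture across the enrolment period. Inclusion began in 2017 and the article expects recruitment to finish in 2023, so many patients will have visit-only data. A simultaneous start in both arms allows the arms to be compared within each capture method, but a pooled fall rate should not be read as if one method had been used throughout.
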